### Inclusion and exclusion criteria

The main inclusion criteria are newly diagnosed type 2 diabetes and/or hypertension. Consecutive primary care patients with suspected type 2 diabetes or hypertension will be screened for inclusion. The diagnose criterion for type 2 diabetes in both the Intervention and the Control groups is defined as a 2 x fasting plasma glucose (fP-glu) ≥ 7.0 mmol/l according to WHO guidelines [28]. The diagnose criterion for hypertension is defined as a resting systolic blood pressure ≥ 140 mmHg or a diastolic blood pressure ≥ 90 mmHg. Hypertension is confirmed by a 24-hour ambulatory blood pressure monitoring: a systolic blood pressure ≥ 135 mmHg and/or a diastolic blood pressure ≥ 85 mmHg is considered confirmatory of hypertension since ambulatory blood pressure is usually a few mmHg lower than office blood pressure [5]. If the resting blood pressure exceeds 160/100 mmHg at two consecutive measurements within one week, the patient will be prescribed pharmacological treatment in addition to physical activity. Patients with a history of type 2 diabetes or hypertension that get diagnosed by the other diagnose will be included in the study as a subgroup, in which a reduction of current medication is one endpoint. On the other hand, patients with a history of type 1 diabetes will be excluded from the study. The overall inclusion and exclusion criteria of the study are presented in Table 1.

**Table 1 T1:** Overall inclusion and exclusion criteria

**A Overall inclusion criteria**	
1. Newly diagnosed type 2 diabetes (a) or hypertension (b) or both	
a) Type 2 diabetes	b) Hypertension
2 x fasting plasma glucose (fP-glu) ≥ 7.0mmol/l	A systolic blood pressure ≥ 140mmHg and/or a diastolic bloodpressure ≥ 90 mmHg, which isconfirmed by a systolic bloodpressure ≥ 135 mmHg or a-diastolic blood pressure ≥ 85mmHg during a 24-hourambulatory monitoring
2. Male and female patients ≥ 18 years	
**B Overall exclusion criteria**	
1. < 18 years	
2. History of type 1 diabetes	
3. Blood pressure > 180/105 mmHg [29]	
3. Known pregnancy	
4. Cognitive disabilities that are likely to limit adherence to intervention	
5. Cardio- or cerebrovascular event that required hospitalization within the past 3 months	
6. Current participation in other clinical study	
7. Severe mental disorder or substance abuse	

### Outcome measures

#### Primary outcome

Level of self-reported physical activity (as assessed with the International Physical Activity Questionnaire (IPAQ) and expressed as MET-minutes).

#### Secondary outcomes

(1) Need of pharmacological therapy for hypertension or type 2 diabetes;

(2) Blood pressure/plasma glucose;

(3) Physical fitness and anthropometric variables;

(4) Mental health (anxiety, depression, sleep, stress);

(5) Health related quality of life; and

(6) Cost-effectiveness of intervention.

### Assessment of physical activity level (primary outcome)

Individual physical activity levels will be assessed with the International Physical Activity Questionnaire (IPAQ), a validated instrument for assessing physical activity [30], in the Intervention group and Control group A. IPAQ comprises 4 simple questions on physical activity, which will be included in the study questionnaire. The IPAQ results will be expressed as MET-minutes per week. A metabolic equivalent, or MET, is a unit that describes the energy expenditure of a specific activity. A MET is the ratio of the rate of energy expended during a specific activity to the resting metabolic rate. 1 MET is equivalent to the resting metabolic rate, while a 2 MET-activity requires two times the metabolic energy expenditure of sitting quietly [31]. If a person does a 2 MET-activity for 30 minutes, he or she has done 2 × 30 = 60 MET-minutes of physical activity.

### Assessment of physical fitness and anthropometric variables (secondary outcome)

Physical fitness will be estimated with the 6-minute walk test in the Intervention group only. The 6-minute walk test measures the distance that a patient can walk on a flat, hard surface in 6 minutes, usually on a short indoor track. This test is useful as a complement to the subjective assessment in the study questionnaire since it evaluates the integrated responses of all body systems that are involved in physical activity including the pulmonary and cardiovascular systems, systemic and peripheral circulation, blood, neuromuscular units and muscle metabolism [32]. In the present study, the 6-minute walk test will be used to evaluate changes in physical fitness expressed as percentage of the individual result at baseline. The patients will perform a “test-walk” for 1 minute before the 6-minute walk test and the test will be performed according to a separate, standardized protocol [32].

Anthropometric measurements will include weight, length, body mass index and waist-to-hip ratio.

### Assessment of behavioural predictors, mental health and health related quality of life (secondary outcome)

With the study questionnaire, psychological variables will be collected to assess a) behavioural predictors, b) mental health and c) health related quality of life. These variables include: a) self-perceived health, self efficacy, self-determination; b) anxiety and depression, stress, panic-related physical sensations, and sleeping quality; c) health related quality of life (Table 2). Almost all these items will be evaluated with questions from already validated questionnaires, which will be included in the study questionnaire. If a person in Control group A gets results that indicates severe depression or anxiety, this person will be offered a medical appointment.

**Table 2 T2:** Study questionnaire variables with references

**Variable**	**Reference**
Demographic and socioeconomic characteristics and other general questions concerning background and health related issues like general health, current medications, symptoms, pain, stress, and sleeping quality.	*The Public Health Survey* in Skåne, Sweden and questions from the Swedish Annual Level of Living Survey (SALLS).
Health related quality of life	EQ-5D (http://www.euroqol.org/)
Lifestyle related habits - general questions related to the individuals: physical activity, healthy eating, tobacco and alcohol usage	The National Board of Health and Welfares Questionnaire.
Physical activity level	International Physical Activity Questionnaire (IPAQ) – short version [30].
Stages of change (readiness for change to be more physically active)	Used in previous study [9]
Physical activity history and dog ownership and dog-walking	Study specific question
Self-efficacy	General Self-Efficacy Scale (http://www.ralfschwarzer.de/)
Self-determination	Perceived Competence Scale (PCS), Health Care Climate Questionnaire (HCCQ), Treatment Self-Regulation Questionnaire (TSRQ) from the Health-Care, Self-Determination Theory Packet (http://www.psych.rochester.edu/SDT/measures/hc_description.php)
Anxiety and depression	Hospital Anxiety and Depression (HAD) Scale [33]
Anxiety related physical sensations	Anxiety Sensitivity Index (ASI) [34]
Activities of daily living (ADL) ability	Canadian Occupational Performance Measure (COPM) [35]
- only patients that score 2–3 p in question A, B, or C in EQ-5D	
Non-adherence and reasons for non-adherence to PARs intervention	Used in previous study [36]

### Assessment of cost effectiveness of intervention (secondary outcome)

The Intervention group will be compared with the two control groups in order to perform cost-effectiveness analysis (CEA) or cost-utility analysis (CUA) or both. All the costs related to the intervention such as training of the personnel and participants’ time and travel costs will be counted. Productivity losses (including informal care) and benefits will be counted using appropriate methods such as the friction cost and the human capital approach [37,38]. The project in general and the study questionnaire in particular, will be designed to effectively capture the benefits of the intervention, for example, the EQ-5D instrument will be used to examine changes in health related quality of life (http://www.euroqol.org). The intermediate outcomes of the intervention (e.g. reduction of cardiovascular risk factors) will be extrapolated by economic modelling (either Decision tree or Markov model) to predict the long term health related benefits [39,40]. Generating estimates of acute and long-term costs associated with the management of diabetes requires information on the annual average health care costs with a wide spectrum of complications. The most significant costs associated with many complications are likely to be those arising from inpatient hospital episodes. These costs have been estimated for selected countries, for example Sweden [41].

### Electronic study questionnaire

The study questionnaire will be filled in directly on a computer at the health care centre under supervision of a health care professional. All data are then submitted to a patient database, which automatically provides instant feed-back on the patients’ health status. The study questionnaire comprises questions from validated question batteries, questions from the regional population survey, and some questions specifically designed for the study (Table 2), in order to thoroughly evaluate the patients’ health status as well as the study methodology. A short-version of the questionnaire will be used at some of the follow-up visits (see Figure 4).

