**Methods/Design:**

The study is designed as a long-term intervention. Three primary care centres are involved in the study, each constituting one of three treatment groups: 1) Intervention group (IG): multi-professional team intervention with PAR, 2) Control group A (CA): physical activity prescription in usual care and 3) Control group B: treatment as usual (retrospective data collection). The intervention is based on self-determination theory and follows the principles of motivational interviewing. The primary outcome, physical activity, is measured with the International Physical Activity Questionnaire (IPAQ) and expressed as metabolic equivalent of task (MET)-minutes per week. Physical fitness is estimated with the 6-minute walk test in IG only. Variables such as health behaviours; health-related quality of life; motivation to change; mental health; demographics and socioeconomic characteristics are assessed with an electronic study questionnaire that submits all data to a patient database, which automatically provides feed-back to the health-care providers on the patients’ health status. Cost-effectiveness of the intervention is evaluated continuously and the intermediate outcomes of the intervention are extrapolated by economic modelling.

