The visit will be based on a team discussion regarding the results of the extended screening including the study questionnaire, the 6-minute walk test and baseline values. It will be structured according to step 2–5 in the 5 A’s model (advise, agree, assist and arrange; Figure 3) to provide the patients with a personal action plan based on individual goals and strategies to overcome personal barriers to physical activity. The initiation visit will be founded on the patients’ present level of motivation for exercise: amotivation, extrinsic motivation or intrinsic motivation, as described in the SDT model (Figure 1). To improve the patients’ autonomy, competence and relatedness regarding a more active lifestyle, the team uses the MI-technique throughout the conversation (Figure 2). It should be noted that all prescribers have attended at least one course in MI*.* The resulting action plan may include referrals to specialists (psychologist, physiotherapist and/or occupational therapist) for individual consultations and treatments to improve internal motivation and/or physical abilities. The discussion will result in a customized PAR, usually prescribed by a psychologist or physiotherapist from the team together with the patient. The PARs will be tailored to fit the patients’ physical and mental condition and motivation, and the recommendations in the Swedish report Physical activity in prevention and treatment of diseases, FYSS, as applicable [27].

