#### Follow-up visits

The patients in the Intervention group and Control group A will return to the clinics for follow-up of the study results regularly (Figure 4). During these follow-up visits, a physical examination, including monitoring of blood pressure and fasting plasma glucose and, if required, a heart- and lung auscultation will be performed. BMI, abdominal and hip circumference will be measured and the patients will fill in the same study questionnaire as before or a short version of the study questionnaire, including questions about their activity level. The patients in the Intervention group will also perform regular 6-minute walk tests.

The multi-professional team will, together with the patient, follow up adherence to the physical activity prescription, and modify it if necessary.

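### The self-reported primary outcome is collected under staff supervision in both prospective arms, but only the Intervention group answers to a goal-setting team, so over-reporting may differ by arm and could not be told apart from real change

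*Protocol article*

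**What the plan says.** All references are to the protocol article.

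- **Outcome.** The only primary outcome is self-reported activity in MET-minutes (Primary outcome). Under Assessment of physical activity level: "IPAQ comprises 4 simple questions on physical activity, which will be included in the study questionnaire". IPAQ is used in the Intervention group and Control group A.
- **Collection.** The section on the electronic questionnaire states: "The study questionnaire will be filled in directly on a computer at the health care centre under supervision of a health care professional". According to the abstract, the database "automatically provides feed-back to the health-care providers" on the patients' health status. Neither statement distinguishes between the arms.
- **Intervention group only.** The initiation visit draws on the baseline questionnaire ("The visit will be based on a team discussion regarding the results of the extended screening including the study questionnaire") and is meant to "provide the patients with a personal action plan based on individual goals and strategies to overcome personal barriers to physical activity". Under Follow-up visits: "The multi-professional team will, together with the patient, follow up adherence to the physical activity prescription, and modify it if necessary".
- **Control group A.** Same baseline examinations and questionnaire, and a usual-care activity prescription where applicable, but no initiation visit, walk test or team opinion.
- **Blinding.** Statistical analysis and power calculation extends it only to the statisticians and researchers who analyse the data.

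**The concern.** A patient who has agreed a personal activity goal, and whose adherence is reviewed by the team that helped to set it, has a reason to report more activity than was done. Supervised on-site completion with feed-back to providers does nothing to relieve that pressure. A Control group A patient fills in the same questionnaire without that team relationship.

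At baseline the Intervention group has no goal yet, because the questionnaire comes before the initiation visit. Any difference in reporting would therefore arise at follow-up, and analysing change from baseline would not remove it. Blinded analysts cannot remove it either, since it enters when the patient answers. If over-reporting is greater in the Intervention group, the excess adds to the primary contrast in the direction of benefit.

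**Working it through.** **1. Where the asymmetry lies.** Set the two prospective arms side by side:

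| Feature | Intervention group | Control group A |
|---|---|---|
| Supervised on-site questionnaire | yes | yes |
| Automatic feed-back to providers | yes | yes |
| Activity prescription | yes, tailored | where applicable |
| Personal goals agreed with a team | yes | no |
| Team review of adherence | yes | no |
| 6-minute walk test | yes | no |

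Supervision and feed-back do not differ by arm. Goal-setting and team review do.

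**2. Is there a check on self-report in both arms?** The walk test, described as a complement to the subjective assessment, is done in the Intervention group only and measures fitness. The general lifestyle questions on activity in Table 2 are self-report within the same questionnaire. Control group B is taken from medical records and has no IPAQ. Blood pressure, glucose, HbA1c, lipids and body measurements are taken in both prospective arms, but they do not measure activity.

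**3. The plan's group sizes.** Inputs from Statistical analysis and power calculation: difference 200, SD 300, power 80%, significance level 5%, loss 30%; 60 and 30 patients at the first analysis. With 2:1 allocation,

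n(control) = 1.5 × [SD × (z_α + z_β) / difference]².

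- One-sided 5%: 1.5 × [300 × (1.645 + 0.842) / 200]² = 20.9, and 41.7 for the Intervention group. Dividing by 0.7 gives 29.8 and 59.6, which matches 30 and 60.
- Two-sided 5%: 27 and 54, or 39 and 78 after allowing for loss, which does not match.

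The sidedness is not stated. That is a separate matter, and both versions are shown below.

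**4. Sensitivity to differential over-reporting.** Let b be the mean excess over-reporting in the Intervention group, in MET-minutes per week, with no true effect. The documents give no value for b, so every value is an assumption. The 200 and 300 are read as per week, the unit given for IPAQ.

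SE = 300 × √(1/60 + 1/30) = 67.1. An observed difference of 1.96 × 67.1 = 131 is significant two-sided (1.645 × 67.1 = 110 one-sided).

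Chance of a significant result favouring the intervention = 1 − Φ(1.96 − b/67.1), with 1.645 in place of 1.96 for the one-sided test:

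| b | b/SE | two-sided 5% | one-sided 5% |
|---|---|---|---|
| 0 | 0 | 2.5% | 5% |
| 50 | 0.75 | 11% | 18% |
| 100 | 1.49 | 32% | 44% |
| 150 | 2.24 | 61% | 72% |
| 200 | 2.98 | 85% | 91% |

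If 30% of 60 and 30 are lost, leaving 42 and 21, SE = 80.2 and the two-sided figures at b = 50 and 100 are 9% and 24%.

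**5. What b means in minutes.** At the 2 MET of the article's own example, 50 to 100 MET-minutes per week is 50/2 = 25 to 100/2 = 50 minutes per week, or about 4 to 7 minutes a day. The full 200 is 100 minutes per week, about 14 a day. At an assumed 3 to 6 MET, the 200 is 67 to 33 minutes per week, about 10 to 5 a day.

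**The case against.** The strongest reply is that the collection procedure treats both arms alike. The asymmetry belongs to the intervention itself and would remain however the questionnaire is administered. Control group A patients may also hold a prescription and also report at the centre that treats them, so the pressure on them is not zero and the difference between arms is unknown. The calculation shows sensitivity to bias, not its likely size. All of this stands.

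A reader might go further and infer that Intervention group patients give their follow-up IPAQ answers directly to the team whose prescription is being judged. The documents do not support that. Nothing says that the supervising professional belongs to the team. The feed-back is described as concerning health status, and nothing says that follow-up IPAQ scores are displayed. The team discussion of the questionnaire is described for the initiation visit, before goals exist. The order of events within a follow-up visit is not stated, and the flowchart is not shown, so some centres may already collect IPAQ first.

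It is also fair that hiding follow-up IPAQ results from the team would carry a cost: the Discussion presents the feed-back system as part of the approach, covering response and adherence to treatment.

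What the reply does not answer is that the procedure as written includes no protection for a self-reported primary outcome where one arm has more reason to over-report. The limitations in the Discussion do not mention it. The Discussion does raise the effect of filling in questionnaires, but as a real change of habits in Control group A, which is different from misreporting.

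**Conclusion.** The concern holds as a risk, not as a demonstrated bias. Desirability pressure may be stronger in the Intervention group at follow-up, and the protocol has no measure common to both arms that could reveal it. It does not follow from the documents that the bias is present, that it favours the intervention by any given amount, or that supervision causes it.

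Modest differential over-reporting would matter. On the assumptions of a normal test, independent patients, SD 300, 60 and 30 analysed and no true effect, an excess of a quarter to a half of the planned difference raises the two-sided false-positive chance in favour of the intervention from 2.5% to about 11–32%. The change is cheap enough to be worth making before follow-up data are collected, because misreporting cannot be separated from real change afterwards.

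**What to change.** Amend the section Electronic study questionnaire so that, at both prospective centres:

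- the follow-up IPAQ is completed by the patient alone, in private, on the computer, before any contact with the treating team or the prescriber at that visit;
- staff give technical help only;
- the instructions are neutral and identical in both arms;
- the answers are locked on submission.

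Feed-back to providers after submission can stay, so this part of the programme is kept.

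Add to the limitations in the Discussion that Intervention group patients know their goals and that their adherence is reviewed, so some differential reporting may remain and cannot be checked against a measure shared by both arms.

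The cost is a small change in visit order and instructions at two centres and a lock on submitted answers. No new instrument or visit is needed. The change reduces the pressure at the moment of answering but does not remove it.

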### Laboratory values

A study specific blood sample, drawn after an overnight fast, and a morning urine sample will be taken at all study-specific visits to measure lipid profile, plasma glucose, HbA1c, haemoglobin, electrolyte status, thyroid status, high-sensitive C-reactive protein and urinary albumin-to-creatinine ratio. The samples will be analyzed at the Department of Clinical Chemistry, Skåne University Hospital. One frozen blood sample will be collected for long-term storage for potential future analysis.

### End of study

The study, including regular data collection, is designed as a longitudinal intervention that will last over years. The patients will be invited to participate in the intervention until further notice or until they choose to finish their participation themselves (not equivalent to non-adherence to intervention).

The intervention may be extended to evaluate other endpoints than the ones described in the present paper. In that case, ethical approval will be applied for separately.

### Adverse events

At the follow-up visits, the patients will be asked if they have experienced any adverse events since the last visit. All adverse events will be reported, independent of possible relation to the intervention.

### Statistical analysis and power calculation

The first statistical analyses and compilation of results will be performed 18 months after inclusion of the first patient or when the Intervention group and Control group A have included and followed up 60 and 30 eligible patients respectively for at least six months. At that point, data will also be collected retrospectively in control group B. Reasons for non-attendance in the study will be analyzed as well as reasons for non-adherence to the intervention. Allocation will be concealed, and study data blinded, for the bio-statisticians and researchers who will perform the analyses.

The sample size is based on an assumed statistical power of 80%, a significance level of 5%, a difference of 200 MET-minutes between the groups, a standard deviation of 300 MET-minutes and a worst-case loss to follow-up of 30%.

The secondary outcomes blood pressure, plasma glucose, need of pharmacological therapy, and cost-effectiveness will be compared between all three study groups.

